# Clinical Assessment of Eye Movement Desensitization and Reprocessing in Memory Distress: Protocol for a Double-Blinded Randomized Controlled Trial

**DOI:** 10.2196/38552

**Published:** 2023-05-12

**Keywords:** EMDR variants, eye movement desensitization reprocessing, flash technique-EMDR, posttraumatic stress disorder

## Abstract

**Background:**

Exposures to “traumatic” events are widespread and can cause posttraumatic stress disorder (PTSD). Cognitive behavioral therapy and eye movement desensitization and reprocessing (EMDR) are frequently used and validated behavioral PTSD treatments. Despite demonstrated effectiveness, highly upsetting memory reactions can be evoked, resulting in extensive distress and, sometimes, treatment dropout. In recent years, multiple treatment approaches have aimed at reducing such upsetting memory reactions to traumatic memories while therapeutic progress proceeds. One of these methods, the flash technique (FT), a modification of standard EMDR (S-EMDR), appears effective in distressing memory reduction. This study will examine FT-EMDR and S-EMDR efficacies when both methods are delivered via web-based video.

**Objective:**

This study aims to assess the relative efficacy of (web-based) FT-EMDR versus S-EMDR in reducing the PTSD symptoms, anxieties, and depression associated with traumatic memories at postintervention and 1-month follow-up.

**Methods:**

This double-blinded, web-based, 2-arm randomized controlled trial will employ self-report outcomes. A total of 90 participants will be identified from the web-based CloudResearch platform and randomly allocated to the experimental or comparison group. Inclusion criteria are as follows: (1) approved for engagement by the CloudResearch platform; (2) 25-60 years of age; (3) residing in Canada or the United States; (4) a recalled disturbing memory of an event >2 years ago that has not repeated and was moderately or more upsetting during occurrence; (5) memory moderately or more upsetting at baseline and not linked to an earlier memory that is equally or more than equally disturbing. Exclusion criteria are bipolar disorder, borderline personality disorder, obsessive-compulsive disorder, schizophrenia, substance abuse or addiction in the past 3 months, suicidal ideation, and suicide attempt in the past 6 months. Interventions include guided video instruction of full FT or guided video of EMDR. Outcome measures are as follows: Primary outcome is PTSD symptoms that are measured by the PTSD Checklist for DSM-5 (Diagnostic and Statistical Manual of Mental Disorders-5) at 1-month follow-up. Secondary outcomes are State Anxiety subscale of State-Trait Anxiety Inventory at baseline, postintervention, and 1-month follow-up; Trait Anxiety subscale of State-Trait Anxiety Inventory; depression (Patient Health Questionnaire-9); and Positive and Negative Affect Schedule measured at 1-month follow-up.

**Results:**

If, at 1-month follow-up, the web-based FT-EMDR intervention is more effective in reducing PTSD symptoms (as measured by the PTSD Checklist for DSM-5) than EMDR, it may help reduce traumatic memory distress in multiple contexts.

**Conclusions:**

This randomized controlled trial will advance current understandings of PTSD symptoms and interventions that target traumatic memory–related distress.

**Trial Registration:**

ClinicalTrials.gov NCT05262127; https://clinicaltrials.gov/ct2/show/NCT05262127

## Introduction

Posttraumatic stress disorder (PTSD) can occur after direct or indirect exposure to traumatic events with frequent symptoms of reexperiencing, avoidance, cognitive-mood alterations, and heightened arousal or reactivity [1]. Traumatic exposures are widespread [2-4], and a study of 2991 Canadian adults indicated that 76% of participants reported one or more traumatic exposures of the type that can lead to diagnosed PTSD [5]. The prevalence of diagnosed PTSD is ~3.9% worldwide and 10% in Canada (~3.7 million people) [5-7]. Disturbing memory retention can lead to diagnosable PTSD, while adversely impacting psychological and physiological well-being [8-10]. Innovative interventions that reduce memory-based disturbance can prevent PTSD diagnoses and improve current status.

Pharmacological PTSD treatments include antidepressants, sympatholytic drugs, antipsychotics, anticonvulsants, and benzodiazepines [11-13]. Despite the availability of these agents, their limited efficacy has motivated adjunctive behavioral interventions [14,15]. A meta-analysis of PTSD treatment indicated that psychological therapies were generally more effective than drug therapies in symptom reduction [14].

Several of the most prominent methods addressing “traumatic” memories are trauma-focused cognitive behavioral therapy, cognitive processing therapy, prolonged exposure, and eye movement desensitization and reprocessing (EMDR) [16-18]. Other exposure-based treatments designed for PTSD are narrative exposure therapy and written exposure therapy [19]. In traditional EMDR, patients follow the horizontal movement of the therapist’s index finger while recalling details of the traumatic memory [20]. The attention devoted to finger movement during recall has been proposed to reduce the intensity and intrusiveness of memory disturbance [20-24]. EMDR is now widely supported as a treatment for PTSD and is being tested for other mental health conditions (eg, generalized anxiety disorders, addiction, and depression) [25,26].

The mechanisms by which EMDR delivers benefits are controversial [27-29] and differ substantially from those proposed for other psychological therapies [30-32]. The divergence maps onto a frequent limitation acknowledged in exposure approaches, namely, traumatic memory confrontation, can generate high arousal levels, emotional distress, dissociation, and treatment dropout [33,34]. The novel variant of EMDR for PTSD investigated in the proposed study, the flash technique-EMDR (FT-EMDR) [35,36], emphasizes, in combination with standard EMDR (S-EMDR) procedures, the use of a positive engaging focus (PEF), which is recalled and imagined while a right-hand-left-hand alternate knee tapping proceeds [35-38]. Although several explanations for the mechanisms mobilized by this method are proposed, their identification is secondary to our goal of assessing efficacy within a double-blinded randomized controlled trial (RCT) that compares S-EMDR with FT-EMDR. If the FT variant demonstrates greater efficacy, mechanism identification and measurement may proceed more clearly.

As FT is a novel EMDR variant, the related research is in its early stages. Nonetheless, our study will follow prior findings that suggest FT efficacy in reducing the distress associated with disturbing memories [35-38]. If efficacy is indicated, one or both approaches could be used in geographic areas that require more immediate treatment needs, such as when warfare or natural disasters evoke traumatic reactions that are more prevalent.

This study has following three objectives: (1) to evaluate whether web-based delivery of FT is more effective in reducing PTSD symptoms than web-based S-EMDR at 1-month follow-up measured by the PTSD Checklist for DSM-5 (Diagnostic and Statistical Manual of Mental Disorders-5) (PCL-5); (2) to assess whether web-based delivery of FT-EMDR is more effective in reducing state anxiety symptoms than S-EMDR at postintervention and 1-month follow-up; and (3) to evaluate whether web-based delivery of FT-EMDR is more effective in reducing depressive symptoms than S-EMDR at postintervention and 1-month follow-up.

## Methods

### Overview

Previous studies of FT-EMDR have indicated that guided in-person FT effectively reduces subjective units of distress caused by distressing memories. These studies were limited due to a lack of randomization and adequate control comparison. This study will be an assessor-blinded, 2-arm (experimental and control) randomized controlled trial, which minimizes placebo effects and implements an adequate sample size and psychometric measurement. This study is expected to have an overall duration of 3 months. The length of study for each participant will be 4 weeks. The recruitment period is estimated to last for 2 months.

### Ethical Considerations

The study was approved by the Research and Ethics Board at York University (087/2020) and is registered with ClinicalTrials.gov (NCT05262127).

### Informed Consent

After eligibility is confirmed by the investigator, web-based informed consent will be obtained from participants. Each participant will review approved informed consent documents where guaranteed privacy and confidentiality protections are specified, along with assurances that all study data will be anonymized and deidentified. Each participant is compensated US $17 for participation. Participants will be informed about the scientific benefits of the study; however, they are informed that their participation is voluntary, and they have the right to terminate their participation at any time. The signed form will be retained as part of the study records.

### Sample Size

#### Overview

With the assistance of the Institute for Social Research at York University, the sample size was calculated for a 3-way repeated measures ANOVA. Sample size calculation was conducted using G*Power 3.1.9.4. The options in G*Power 3.1.9.2 were as follows: (1) test family: “*F* test”; (2) statistical test: “ANOVA: Repeated measures, between factor interaction”; and (3) type of power analysis: “A priori: Compute required sample size–given α, power, and effect size.” An a priori power analysis was completed using a moderate effect size (*F*=0.25), 0.8 power (1β error probability), and an α error probability at *P*<.05. G*Power 3.1.9.4 determined that a minimum sample size of 37 participants per group provides ample testing power. Considering a 20% (n=7.4) oversampling to account for potential participant dropout and experimental error, a proposed minimum sample size of 44 per group is deemed adequate to detect within-group and between-group differences based on a repeated measures design.

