### Hypotheses

FT-EMDR (the experimental condition) will be significantly more effective than S-EMDR in reducing self-report scores on the PCL-5 at 1-month follow-up to the intervention than traditional EMDR.

FT-EMDR (the experimental condition) will be significantly more effective than S-EMDR in reducing self-report scores on the S-STAI at postintervention and 4-week follow-up than traditional EMDR.

FT-EMDR will be significantly more effective than S-EMDR in decreasing self-report scores on the PHQ-9 at 1-month follow-up.

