### Statistical Analyses

Statistical analysis will include the calculation of descriptive statistics for demographic and psychological characteristics at baseline, postintervention, and the follow-up period. Study outcomes will be presented as means and SDs for numeric variables and frequencies and percentages for categorical variables. In addition, potential between-group differences at baseline will be evaluated using *t* tests for numeric variables and chi-square tests of independence for categorical variables. Significance will be set at *P*≤.05 and will be presented with *r* values for each questionnaire.

To evaluate the effects of the intervention on primary study outcome (PCL-5) and secondary outcomes (PHQ-9, S-STAI, Trait Subscale-State-Trait Anxiety Inventory, PANAS-Positive, and PANAS-Negative), linear mixed models (LMM) will be employed with an AR (1) covariance structure and random intercepts for each study participant to allow for both fixed and random effects. The LMM assumes that the outcome measure is normally distributed. All models will include adjustments for age and sex (among other psychological characteristics). Statistically significant group×time interactions, indicating between-group changes in outcomes, will be followed by simple main effect evaluation. Cohen d effect sizes for between-group and within-group comparisons will also be calculated according to procedures outlined in Lakens [47]. All analyses will be conducted using RStudio [48] and associated statistical packages, including nlme [49], psych [50], and ggplot2 [51].

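### The stated 80% power and 37 per group are not established for the primary comparison, the group × time test of PCL-5 at baseline and 1 month

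*Protocol article*

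**What the plan says.** In the protocol article, Methods, Sample Size (Overview), "the sample size was calculated for a 3-way repeated measures ANOVA". The G*Power option is given as "ANOVA: Repeated measures, between factor interaction", run "using a moderate effect size (*F*=0.25), 0.8 power (1β error probability), and an α error probability at *P*<.05". The conclusion is that "a minimum sample size of 37 participants per group provides ample testing power". The allowance for loss follows: "Considering a 20% (n=7.4) oversampling to account for potential participant dropout and experimental error, a proposed minimum sample size of 44 per group", which the section calls adequate for both within-group and between-group differences. The abstract plans a total of 90.

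The first hypothesis is that FT-EMDR does better than S-EMDR in "reducing self-report scores on the PCL-5 at 1-month follow-up". The Figure 1 legend lists PCL-5 at baseline and follow-up but not immediately after the intervention, so the primary outcome has two occasions. Statistical Analyses plans a linear mixed model in which the group × time interaction carries the between-group difference in change.

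The section does not give the number of measurements or the correlation entered, nor a PCL-5 SD or target difference.

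**The concern.** The sized effect and the tested effect do not visibly match. The trial as described has two factors, group and time, yet the calculation is called 3-way. The option label blends two G*Power procedures, the between-factors test and the within-between interaction, which need very different sample sizes at the same f. The word moderate is attached to f = 0.25 without saying what that means for PCL-5 at 1 month.

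The two arms are described in the Discussion as nearly identical apart from the positive engaging focus, so a null result is a realistic outcome. A reader relying on the Sample Size section would take such a result as adequately powered evidence against a moderate difference, and the document does not support that.

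**Working it through.** **Inputs from the article.** f = 0.25, α = 0.05, power 0.80, 37 per group (74 in total), 90 planned, PCL-5 at two visits. **Assumed because not given:** two groups (k = 2) in the calculation, 1:1 allocation, equal SDs at both visits, and a baseline to follow-up correlation ρ of 0.3 to 0.7, with 0.8 as a further check.

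**1. Reproducing 37 per group.** Noncentral F, with N the total and m the number of occasions:
- between factors: λ = f²·N·m / [1 + (m − 1)ρ], df k − 1 and N − k;
- interaction: λ = f²·N·m / (1 − ρ), df (k − 1)(m − 1) and (N − k)(m − 1).

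| Total N needed | m = 2 | m = 3 |
|---|---|---|
| Between factors, ρ = 0.5 | 98 | 86 |
| Interaction, ρ = 0.5 | 34 | 28 |
| Interaction, ρ = 0 (its largest value for ρ ≥ 0) | 66 | 54 |

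The two-group interaction never needs more than 66, so 74 cannot come from it. Two alternative definitions of λ for the interaction, f²·N·(m − 1) and f²·(N − k)·(m − 1), give 128 to 130 at m = 2 and 80 to 82 at m = 3, again not 74. The between-factors test does give 74, at m = 2 with ρ about 0.13 (λ = 0.0625 × 74 × 2 / 1.13 = 8.19) or at m = 3 with ρ about 0.35 (λ = 0.0625 × 74 × 3 / 1.70 = 8.16). That test averages over occasions, including baseline, where randomisation makes the expected difference zero.

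**2. What f = 0.25 means for PCL-5.** Take two groups, two visits, SD 1, equal baselines and a 1-month difference D. The cell means are 0, 0 and 0, −D. The interaction deviations are all ±D/4, so the interaction f = D/4. The group means are 0 and −D/2, so the group f is also D/4. Hence f = 0.25 gives D = 4 × 0.25 = 1.0 SD, and D = 0.5 SD corresponds to f = 0.125. This step needs no correlation.

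**3. Power for D = 0.5 SD at 1 month.** With two complete visits, group × time is the change-score comparison. Noncentral t, two-sided 5%, n per arm:
- change: ncp = 0.5 / √[2(1 − ρ)] × √(n/2);
- baseline-adjusted: ncp = 0.5 / √(1 − ρ²) × √(n/2).

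For n = 37 and ρ = 0.5, the change ncp is 0.5 / 1 × √18.5 = 2.15, which gives 56%. A 1-month comparison that ignores baseline also has 56%.

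| 37 evaluable per arm | ρ = 0.3 | 0.5 | 0.7 | 0.8 |
|---|---|---|---|---|
| Group × time (change) | 43% | 56% | 78% | 92% |
| Baseline-adjusted | 60% | 69% | 84% | 94% |

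**4. Correlation needed for 80% at 0.5 SD.**

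| Evaluable per arm | Change | Baseline-adjusted |
|---|---|---|
| 37 | about 0.71 | about 0.65 |
| 45 (all 90, no loss) | about 0.65 | about 0.55 |

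The second row is an upper bound. The plan's own 20% loss would leave 45 × 0.8 = 36 per arm.

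**5. Difference detectable with 80% power, 37 per arm.** At ρ = 0.5 the change comparison detects 0.66 SD. Scaling by √[2(1 − ρ)]: 0.66 × 1.183 = 0.78 SD at ρ = 0.3, and 0.66 × 0.775 = 0.51 SD at ρ = 0.7. Baseline-adjusted, scaling by √(1 − ρ²) gives 0.63, 0.57 and 0.47 SD at ρ = 0.3, 0.5 and 0.7.

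**The case against.** The strongest reply is that the document does not show the power to be below 80%. A reader might infer from the figures at ρ = 0.5 that the trial lacks 80% power for a moderate difference. That inference is not supported: no baseline to follow-up correlation is given, at ρ = 0.8 the power is above 90% by either analysis, and the 90 planned participants lower the threshold further if few are lost. This stands.

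A reader might also conclude that 37 is an arithmetic error. That is not shown either. An article may leave out the number of occasions and the correlation entered, and the between-factors test reaches 74 at plausible values of both. Failure to reproduce at ρ = 0.5 tests only an assumed input.

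The labels may simply be loose. 3-way could refer to three assessments, which S-STAI has, and the option may have been meant as the within-between interaction, the right kind of test for Statistical Analyses. The intention cannot be settled from the text. But if the interaction was meant, 74 does not come from it, and f = 0.25 is still a 1.0 SD difference at 1 month for PCL-5.

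The planned adjustment for age, sex and other characteristics might add some precision, but nothing in the document lets that be quantified. Finally, nothing here undermines the adequacy claim for within-group differences: a paired change of 0.5 SD at ρ = 0.5 needs about 34 per group, so 37 suffices.

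**Conclusion.** The point holds as a failure to establish the stated power. The 80% and the 37 per group are not shown to belong to the primary PCL-5 contrast, and with two groups the total of 74 is incompatible with the group × time interaction at f = 0.25 and any non-negative correlation. The effect labelled moderate is a 1.0 SD difference at 1 month when baselines are equal, twice the 0.5 SD usually called moderate for a two-group difference.

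For 0.5 SD and 37 evaluable per arm, group × time power runs from 43% to 78% over correlations of 0.3 to 0.7, and 80% needs about 0.71 or more. These power figures rest on equal SDs at the two visits, complete pairs and an assumed correlation. The upper limit of 66 and the 1.0 SD equivalence do not depend on any particular correlation.

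**What to change.** Replace the power statement with one for the planned test, for example: *With 37 evaluable per group and a two-sided 5% level, the group × time test of PCL-5 has 80% power for a difference of 0.66 SD at an assumed baseline to follow-up correlation of 0.5 (0.78 SD at 0.3, 0.51 SD at 0.7).* Translate this into PCL-5 points with a stated SD and its source.

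Quote 0.57 SD (0.63 to 0.47 SD) only if the primary model is specified as baseline-adjusted. The written plan judges group × time and does not name baseline PCL-5 as a covariate, so that figure would be too favourable for it.

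Remove the word *ample* and the claim that the size is adequate for moderate between-group differences. The within-group claim can stay.

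The cost is text only, with no extra enrolment. The stated sensitivity becomes less favourable, and a null result can then be read against the difference the trial could detect.

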#### Inclusion Criteria

Participants must pass the CloudResearch platform’s standardized assessment of *attention*, *engagement*, and *language comprehension* for study participation [39]. Language comprehension and engagement are assessed by identifying synonyms, reading articles, and answering comprehension questions. Additional attentional competencies are assessed by evaluating factual correctness in answers to demographic questions (eg, “I work 28 hours in a typical workday”). In addition, the CloudResearch platform screening is based on a recorded history of providing high-quality data in prior study participation.

In the investigator-based criteria, participants must (1) be between 25 and 60 years of age and maintain residence in the United States or Canada; (2) be able to identify a memory regarding an event that occurred more than 2 years ago and has not been since repeated; (3) identify the memory as moderately upsetting, or more than moderately upsetting, when it occurred; (4) clearly recall the identified memory; (5) find the memory to be still moderately upsetting, or more than moderately upsetting, when recalled; and (6) identify the memory as not tied to an earlier memory that is equally or more disturbing.

Since participants are exposed to only 1 brief session, processing a series of upsetting memories is unreasonable and potentially harmful. Hence, the inclusion of only a single distressing memory, which should be distant from the participation date, was carefully implemented to minimize emotional arousal.

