#### Exclusion Criteria

Exclusion criteria are as follows: (1) individuals who disclose a past or present self-reported diagnosis of bipolar disorder, borderline personality disorder, obsessive-compulsive disorder, schizophrenia, or a substance abuse or addiction in the past 3 months; and (2) individuals who disclose having suicidal ideation or who have attempted suicide in the past 6 months prior to the study.

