### Outcome Measures

#### Primary Outcome

The primary outcome measure will be the PCL-5 [42]. It is a 20-item self-report instrument measuring the presence and severity of PTSD symptoms. Each item is rated on a 5-point Likert scale ranging from 0 (not at all) to 4 (extremely), indicating how much each symptom has bothered the respondent in the past month. Higher scores indicate more severe PTSD-like symptoms, and a score higher than 31-33 alerts to a possible PTSD diagnosis.

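### Entry sets no minimum PCL-5 score, so people with few symptoms can enrol, and any treatment difference on the primary outcome is attenuated for them

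*Protocol article*

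**What the plan says.** Inclusion Criteria in the Protocol article set severity on the memory alone. It must have been at least moderately upsetting when it happened, and the participant must still "find the memory to be still moderately upsetting, or more than moderately upsetting, when recalled". The section adds that "the inclusion of only a single distressing memory, which should be distant from the participation date, was carefully implemented to minimize emotional arousal". Exclusion Criteria remove "individuals who disclose a past or present self-reported diagnosis of bipolar disorder, borderline personality disorder, obsessive-compulsive disorder, schizophrenia", recent substance abuse and suicidality. Neither list, nor the shorter version in the Abstract, asks for a PTSD diagnosis, a symptom level or a PCL-5 score.

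Under Primary Outcome, "The primary outcome measure will be the PCL-5", and "It is a 20-item self-report instrument measuring the presence and severity of PTSD symptoms", with items scored 0 to 4. The only threshold is descriptive: "Higher scores indicate more severe PTSD-like symptoms, and a score higher than 31-33 alerts to a possible PTSD diagnosis". Under Hypotheses, FT-EMDR is to be "significantly more effective than S-EMDR in reducing self-report scores on the PCL-5 at 1-month follow-up". The Figure 1 legend lists PCL-5 at baseline and at follow-up, as a measure and not as an entry test. Sample Size uses f = 0.25 and gives no PCL-5 mean or SD. Statistical Analyses plans a mixed model read through the group-by-time interaction, adjusted for age, sex and unnamed psychological characteristics.

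**The concern.** The entry rule selects on distress at one memory. The endpoint needs room to fall on a 20-item symptom scale. Nothing in the article links the two, so someone with one upsetting memory and very few PTSD symptoms qualifies. At the floor such a person cannot improve on the scale. Near it, the possible improvement is cut short in both arms, and the contrast between arms shrinks. Randomisation keeps the comparison unbiased but does not restore the lost power. The eligibility list is fixed in this document, so an analysis plan could soften the problem but not remove it.

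**Working it through.** **1. Scale.** 20 items x 4 = 80 at most, and 20 x 0 = 0 at least.

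**2. Room needed.** For two groups d = 2f = 2 x 0.25 = 0.50. The difference in points is 0.50 x SD. The SD is not given. Assumed values of 10, 15 and 20 give 5, 7.5 and 10 points. Unless the comparison arm worsens, the FT-EMDR arm must fall by at least that much. A participant who starts below it cannot do so.

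**3. The plan's own figure.** The 37 per group (74 in total) cannot be reproduced uniquely, because the number of measurements m and their correlation rho are not stated. With a between-groups test, noncentrality N f² m / (1 + (m - 1) rho), a total near 74 arises at m = 3 with rho about 0.35 (70 at 0.3, 78 at 0.4), or at m = 2 with rho about 0.1-0.2 (72-78). This is a separate matter. Here 37 evaluable per arm is taken as given.

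**4. Constant effect with a floor.** Assumptions: latent SD 15, baseline to follow-up correlation 0.5, true difference 7.5 points, whole scores held within 0-80, 1-month score compared with baseline as covariate, two-sided 0.05, 4,000 replicates. Check without a floor: 7.5 / (15 x √(1 - 0.5²)) = 7.5 / 12.99 = 0.577, which gives 69% power, in line with the simulated 67-69%.

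| Latent baseline mean | Baseline scores at 0 | Observed difference (points) | Power with floor | Power without | Loss (points) |
|---|---|---|---|---|---|
| 5 | 38% | 4.0 | 53.1% | 67.5% | 14.4 |
| 10 | 26% | 5.0 | 59.6% | 69.0% | 9.4 |
| 15 | 17% | 5.8 | 62.9% | 67.6% | 4.7 |
| 20 | 10% | 6.4 | 65.5% | 67.5% | 2.0 |
| 30 | 2% | 7.2 | 66.9% | 68.2% | 1.3 |
| 40 | 0.4% | 7.5 | 68.8% | 67.3% | none |

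The simulation error of each power is about √(0.6 x 0.4 / 4000) = 0.8 points. The observed mean lies slightly above the latent one: at latent 15 it is 15 x 0.841 + 15 x 0.242 = 16.2.

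**5. Proportional effect.** Assumptions: gamma-distributed baseline, true falls of 40% versus 20% (SD 0.35), measurement noise SD 5, scores held within 0-80, 37 per arm. PCL-5 is taken only twice, so with complete data the group-by-time test amounts to comparing change.

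| Assumed baseline mean (SD) | Change, no minimum | Change, minimum 20 | Gain (points) | Baseline-adjusted, no minimum |
|---|---|---|---|---|
| 12 (11) | 17% | 45% | 28 | 23% |
| 18 (14) | 24% | 51% | 27 | 32% |
| 25 (16) | 36% | 48% | 12 | 41% |

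Repeat runs without a minimum gave 16-18%, 24-26% and 33-36%. At an assumed mean of 35 the minimum still moves power from 46% to 51%. Baseline adjustment alone adds 6, 8 and 5 points in the three rows.

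**The case against.** The strongest reply is that the premise is unmeasured. No baseline PCL-5 mean, SD or distribution is given, so the share of participants near the floor is unknown. That stands, and it limits what can be claimed. A reader might infer several stronger things that the article does not support:

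- *That f = 0.25 is unattainable in this sample.* This is unproven. f is standardised, and a milder sample may also vary less.
- *That the normality condition fails.* The article does say "The LMM assumes that the outcome measure is normally distributed", but a pile-up of scores at zero is only possible, not shown.
- *That the 10% PTSD figure in the Introduction shows a low-scoring sample.* It is the prevalence of diagnosed PTSD in Canada. Enrolled people must have a memory that still upsets them.
- *That a null result could not be told from a floor effect.* Baseline PCL-5 is collected and will be summarised, so a low baseline would be visible.

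The size is also easy to overstate. If a share q has no room to fall, simple dilution, d = 0.50(1 - q), takes the power of a t-test with 37 per arm from 56% at q = 0 to 32% at q = 30% and 25% at q = 40%. That gives the low scorers the full SD of change. If they vary less, power is 35-41% and 28-36%. The drop from the planned 80% to 56% comes from using a simple t-test and has nothing to do with the floor. In step 5 the effect grows with baseline by construction, so the gain from a minimum is not purely a floor effect.

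Finally, the mild population looks deliberate. The Introduction speaks of preventing PTSD diagnoses, Inclusion Criteria give a safety reason for a single distant memory, and the Discussion calls the data preliminary. This explains the choice of memory. It does not explain why a fall in PTSD symptoms is the primary outcome with no check that there are symptoms to reduce.

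**Conclusion.** The point holds in a limited form. The entry criteria allow low PCL-5 scorers into a trial whose primary outcome is a greater fall in PCL-5, and nothing elsewhere in the article repairs this. The effect is attenuation: complete at a score of 0, partial just above it.

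How much power is lost cannot be fixed from the document. Under the assumptions shown, the loss is material if mean baseline PCL-5 is roughly 18 or lower. With a constant effect it is about 5 to 14 points at latent means of 15 down to 5; with proportional falls more is at stake. At a mean of about 30 or above it is small. The direction is the same in both models, but the size rests on assumed baseline distributions and on the form of the effect. The change is worth making. The article does not show that the trial must fail without it.

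**What to change.** 1. **Entry.** Give the existing PCL-5 at the screening step before randomisation, and require a prespecified minimum total that leaves room for the assumed effect. The sponsor chooses the value; 20 above is only an illustration. Informed Consent now places consent after eligibility is confirmed, so consent must move ahead of this questionnaire. The costs are more screening (streaming recruitment admits one person per slot), a narrower population, and regression to the mean in the planned within-group effect sizes. No extra participants are needed.

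2. **Analysis, in any case and for anyone already enrolled.** Make 1-month PCL-5 adjusted for baseline PCL-5 the primary between-arm comparison, instead of relying only on the group-by-time change. Report the arm-by-baseline interaction as supportive. Do not make the arm difference at a score of 33 primary, because it is imprecise if few participants score that high. This uses data already planned and costs nothing to collect. It recovers only part of the loss.

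3. **Conclusion.** Report the baseline PCL-5 distribution and limit the claim to the symptom range actually enrolled.
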